Any woman who expresses interest will be telephoned by the principal researcher. The principal researcher will ensure all the participants understand the detailed study information they have been given. They can also discuss the study and any questions they might have with the principal researcher. Following the call, they will still have time to consider whether to participate in the study before their 24 gestational week antenatal appointment. If they agree to participate in the programme, they will be scheduled a date before 24 gestational weeks to meet the principal researcher, and written informed consent will be obtained. If the participants withdraw their interest before providing consent, recruitment will continue until there are enough potential participants. The time for recruitment and randomization will be extended to ensure enough participants are recruited for the study. After the participants have signed the consent form, they will meet the research midwife in another office in the hospital and complete the baseline data.

The participants will be randomly allocated to the usual antenatal care or group-based PFMT programme by using a computerized block randomization programme which is generated by the principal researcher (the size of the block is 16). Allocation will be concealed by using sealed opaque envelopes. The envelope will be offered to the participants in sequence by the midwife. They will complete the baseline assessment after randomization. The participants who are randomized to the group-based supervision group will then be scheduled a date by the midwife for the first group training session. The flowchart of the feasibility study and the flow for participants is presented in Additional file 2. According to the inclusion and exclusion criteria, 75% of the pregnant women are estimated to be eligible [32, 33]. Therefore, the recruitment is expected to be completed within 3 months, and the screening of the pregnant women will stop when 48 participants have been recruited. No reimbursement was provided for women consenting to participate or continue participating in this study.

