### Blinding

It is not possible for the midwife delivering the intervention to be blinded to the pregnant women in the intervention groups or the usual antenatal care group. Also, the principal researcher will not be blinded to the participants to be invited in the interviews post-intervention. However, the principal researcher, who will be conducting baseline and follow-up data analysis, will be blinded to the allocation when analysing the feasibility data.

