All the group-based training sessions in the programme will be provided by one midwife to ensure consistency. The midwife will be trained beforehand by the principal researcher about the PFMT programme. The participants will be required to meet the midwife for group supervision once a month on the day of their regular antenatal check for consecutive four consecutive months (approximately 24 gestational weeks, 28 gestational weeks, 32 gestational weeks and 36 gestational weeks). The group supervision sessions will last for about 45 min which include attendance registration and progress review (5 min), education on the causes of UI and PFMT (10 min), skills training in sitting and standing positions (20 min), discussion on what is taught (8 min) and reminder about the next session (2 min). The registration of attendance and the training diary which will be provided to the participants after each session will be monitored to record adherence to the programme. Women who attend at least 75% of the supervision sessions will be considered as adherent. Motivation to maintain PFMT will be emphasized by the midwife and supported by WeChat groups which will be limited to the eight pregnant women in the group session. A reminder to practise PFMT as well as the audio instructions on doing PFMT will be sent automatically in the WeChat group twice a day. In addition, leaflets on PFMT, training diaries and stickers which motivate the participants to undertake PFMT will be provided. The PFMT leaflets and training diary were provided as Additional file 3. One day before the next session, a reminder of the session date will be sent to the WeChat group. The participants will be encouraged to discuss any topics related to PFMT and UI in the WeChat group to facilitate peer support. The midwife and the principal researcher will adopt administrative roles and monitor the WeChat groups but will not answer questions or participate in discussions. Any problems which the pregnant women encountered during the exercises will be addressed during face-to-face supervision. There will be ground rules set for the groups, for example, the women in the groups need to keep the information confidential within the group and treat each woman in the group with respect. If any women break the ground rules or discuss information in the WeChat group that is unsafe, the principal researcher will remind the women about the ground rules and correct any information that is dangerous. During the development of this study, the barriers identified from the systematic review [13], survey [24] and discussion with stakeholders, such as time commitment, forget to continue PFMT were mapped to the COM-B model and explored in a separate study. For reasons of equipoise, women in the comparator group will be offered the group-based PFMT intervention at the end of the study if they wish.

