	Ambiguities regarding eligibility criteria
	Reasons for ineligibility
Data collection	Numbers of missing items in the collected questionnaires
Attrition	Rates of dropout
Resources needed to complete the study and the intervention	Length of time required for participants to complete questionnaires, interviews and exercise diary
Participant adherence	Numbers of attended sessions
	Numbers of exercise at home
Participants’ acceptability and satisfaction with intervention	Reasons for poor attendance
	Experience of attending the intervention

Besides the outcome measures which assess the acceptability of the programme, the UI outcome measures include self-reported UI and UI severity will be assessed by ICIQ-SF (a validated questionnaire which both assesses the severity of urinary loss and quality of life impact) [37]. The adherence to the programme will be assessed by attendance records from the group-based training sessions and completion of a training diary which includes the frequency and duration the participants self-report doing the exercises. The number of PFMT exercises at home was recorded in the training diary to assess participants’ adherence to home training. The training diary will be submitted to the principal researcher after the training sessions.

The UI outcome measure has been reviewed and approved by stakeholders (phase 1) and will take a total estimated completion time of 5–10 min on each occasion. Baseline outcome measures include demographics (name, date of birth, education level, body mass index and contact details) and will be collected after obtaining informed consent from the participants. The schedule for assessments is shown in SPIRIT figure [21] (Fig. 2).

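### The principal researcher both generates the allocation sequence and enrols the women, and the statement that this person analyses the data blinded contradicts the protocol's own procedures

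*Protocol article*

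**What the plan says.** All references are to the protocol article.

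- **Sequence.** The section *Recruitment, consent, assessments, randomization and allocation concealment* describes a "computerized block randomization programme which is generated by the principal researcher (the size of the block is 16").
- **Enrolment.** The same section says: "Any woman who expresses interest will be telephoned by the principal researcher". The researcher checks that the woman understands the study and discusses her questions. Women who agree then have a meeting arranged: "they will be scheduled a date before 24 gestational weeks to meet the principal researcher, and written informed consent will be obtained".
- **Concealment.** "Allocation will be concealed by using sealed opaque envelopes". The midwife, in a different office, offers them in sequence.
- **Blinding.** The *Blinding* section says that the principal researcher, who analyses the baseline and follow-up data, "will be blinded to the allocation when analysing the feasibility data". It also says that this person is not blinded to the women invited to interview.
- **Contact with the intervention arm.** *Interventions*: "The midwife and the principal researcher will adopt administrative roles and monitor the WeChat groups". Each WeChat group is restricted to the eight women of one training group. *Measures*: "The training diary will be submitted to the principal researcher after the training sessions". *Measures* also has the principal researcher choose six to eight intervention women for the focus group, partly on how well they adhered, and run that focus group.

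**The concern.** Two separate problems arise from one person holding several roles.

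First, allocation concealment is meant to ensure that whoever enrols a participant cannot foresee her allocation. An envelope cannot do that for the person who wrote the sequence. Someone who knows what comes next can, without intending to, press harder or less hard for consent, or influence the order in which women enter.

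Second, a report following this plan would describe a blinded analysis that its own procedures rule out. A reader of the results, or a funder of the definitive trial, would rely on a safeguard that was not there.

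What is exposed is the between-arm comparison of UI outcomes and the enrolment procedure itself, which the study is rehearsing for the definitive trial.

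**Working it through.** The point concerns roles, so most of the check sets the statements side by side. The one figure involved is the block size.

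**1. Block size against the design.** Inputs: 48 women, 24 per arm (*Sample size*); block of 16 (*Recruitment, consent…*); training groups of eight (*Interventions*).
- Blocks: 48 / 16 = 3.
- Per block at 1:1: 16 / 2 = 8 per arm.
- Per arm: 3 × 8 = 24, which makes 24 / 8 = 3 training groups.

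The block size agrees with the rest of the plan, and nothing here requires changing it.

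**2. Who can foresee an allocation at enrolment?**

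| Step | Person | Could know the next allocation? |
|---|---|---|
| Screening, information sheet | Clinic midwives and nurses | No |
| Generating the sequence | Principal researcher | Yes, as its author |
| Telephone call, questions, consent meeting | Principal researcher | Yes, if the list is kept or remembered |
| Handing out envelopes after consent | Midwife | Envelopes are sealed |

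The third row is the gap. The article names no independent holder of the list and does not say who prepares the envelopes. The number of foreseeable allocations therefore lies between 0 of 48 (list generated and never seen again) and 48 of 48 (list kept and consulted). The documents do not place it within that range.

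**3. Can the analyst be blinded?** The *Blinding* statement has to be compatible with each of the following:
- The analyst generated the sequence (*Recruitment, consent…*).
- The analyst is an administrator of WeChat groups that contain only intervention women, and so can see who belongs to them (*Interventions*).
- The analyst receives diaries that intervention women keep (*Measures*).
- The analyst selects intervention women by adherence and attendance, and meets them in the focus group (*Measures*).

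The statement is incompatible with these. The feasibility data also identify the arm. The adherence criteria in *Measures* have a denominator of one arm: 18 / 24 = 75% attending at least 3 / 4 = 75% of sessions, and 18 / 24 = 75% recording home exercise twice daily. Any record with attendance or diary entries is therefore an intervention record.

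**4. Does number-coding help?** *Data management and confidentiality* replaces names with numbers. That protects identity, not allocation: a number with attendance or diary data attached still shows its arm. No one is named to mask the arms.

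**5. What depends on it?** The quantitative progression criteria are the share of eligible women who consent (at least 50%), pooled questionnaire return (40/48 = 83%, 38/48 = 79%, 36/48 = 75%) and intervention-arm adherence (18/24). None is a contrast between arms. The planned between-arm analysis of UI outcomes, with confidence intervals, is such a contrast (*Analysis of quantitative data and qualitative data*).

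**The case against.** The strongest reply is that the article describes real safeguards. Clinic staff screen, women decide at home and make the first contact themselves, and after consent a different person in another office issues sealed envelopes. The text does not say that the principal researcher keeps the list or has it to hand when taking consent, and an article may leave such detail to the full protocol. This stands as far as it goes. A reader might infer that concealment is broken; the documents do not support that. They support only that the allocation is not protected from the person who enrols.

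A reader might also blame the fixed block of 16. That is not the source of the problem. The author of the list has no need to guess, the midwife who sees allocations meets women only after consent, and the block size suits groups of eight.

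Nor does the principal researcher deliver the intervention. One midwife gives every session, and the WeChat role is mainly monitoring. This narrows the contact to group administration, diary receipt and the focus group, which is still enough to reveal allocation.

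On blinding, it can be said that the article admits unblinding for the interviews, that the UI outcome is self-reported by questionnaire, and that the tests are named, so an unblinded analyst has limited scope to alter results. That limits the harm. It does not make the sentence true.

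Finally, the *Discussion* says that the data will not be used to assess effectiveness, and the analysis section limits the between-arm comparison to obtaining standard deviations and a sample size. This stands, and it lowers the severity. However, the same section also presents the comparison as a way to judge whether the intervention looks promising.

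**Conclusion.** The concern holds in two parts. Sequence generation is not separated from enrolment, so sealed envelopes do not protect the allocation from the person who enrols. The statement that this person analyses the feasibility data blinded is wrong as written, because it conflicts with the recruitment, intervention and measurement procedures and with data that exist in one arm only.

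The first part assumes that nothing in the full protocol removes the list from the principal researcher; if something does, that exposure falls towards zero. The second part rests on the article's text alone and does not need that assumption. The size of any bias cannot be estimated from the documents, and none is shown to have occurred.

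This should be fixed, but it does not invalidate the study. No progression criterion is a between-arm contrast and effectiveness is not assessed. What remains exposed is the UI comparison, the accuracy of the report, and the procedures carried into the definitive trial.

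**What to change.** 1. Have a colleague with no participant contact generate and hold the list and prepare the sealed envelopes. Keep the three blocks of 16, so sample size, ratio and group size are unchanged. Name that role in the recruitment section.
2. Replace the sentence in *Blinding* with a plain statement that the principal researcher is not blinded. Alternatively, have a colleague run the between-arm UI analysis from an arm-coded file that contains no attendance or diary data, and limit the blinding claim to that analysis.

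The cost is the revised wording and, by assumption, a few hours of a colleague's time; the documents give no figure. The article says that recruitment had not started at submission. If it has started since, the second change can still be made in full.

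Randomising 16 women at once is not needed for this fix. At even accrual of 48 women in 3 months a batch would take 16 / 48 × 3 = 1 month to fill, which could delay allocation when consent is taken just before 24 weeks and the first session falls at about 24 weeks.

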### Study design

This single-centred, three-phased study uses a mixed methods research design guided by the MRC [18] and behaviour change wheel (BCW) frameworks [20]. The use of these validated frameworks within the feasibility study will be published separately in a co-design paper. This trial will comprise a two-arm feasibility RCT, in which participants will be randomly allocated to either group-based PFMT or usual antenatal care. Participants will be assessed at three time points during the study: baseline (24 gestational weeks), post-intervention (approximately 36 gestational weeks) and follow-up assessment (42 days after delivery). This study has been approved by the ethics committees of King’s College London (LRS/DP-21/22–26,714) and Nanjing Maternity and Child Health Care Hospital (2021-KY-084) and has been registered with ClinicalTrials.gov under NCT05242809. This study has been designed following the Standard Protocol Items: Recommendations for Interventional Trials (SPIRIT) [21] and reported according to the Consolidated Standards of Reporting Trials (CONSORT) extension for pilot and feasibility trials statement [22]. The SPIRIT checklist is presented as the Additional file 4: Table S1. The study flow diagram is presented in Fig. 1.

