### Recruitment, consent, assessments, randomization and allocation concealment

The principal researcher will provide details of the study to the midwives and nurses who run the Nanjing Maternity and Child Health Care Hospital antenatal clinics. The midwives and nurses will be responsible for giving information about this study to the women. The midwives and nurses will screen potential participants based on the inclusion criteria to determine whether they are eligible to take part in the study when they attend the antenatal clinics at around 19–20 gestational weeks. If the participants are eligible to take part in the study, the midwives and nurses will provide participants with an information sheet. The midwives and nurses will be trained before speaking to women to assess eligibility for the study, and the midwives and nurses will inform the potential participants that the questions are asked only for assessing whether they are eligible for the study; this information will not be recorded in their medical records. Potential participants will be informed that choosing not to take part in or withdrawing from the study will not affect the care, treatment or service they receive in any way. They may also choose not to take part in the study or withdraw from the study at any time without giving a reason.

Potential participants will not need to tell the midwives and nurses whether they want to take part in the study at the time. They will take the information sheet home to consider whether to take part in the study or not before they attend their next antenatal clinic appointment at around 23–24 gestational weeks. If the participants are willing to participate in the study, they will be asked to contact the principal researcher using the contact information on the information sheet before their next antenatal appointment.

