**Fig. 2 Fig2:**
[figure not shown]
The schedule of enrolment, interventions and assessments

For the feasibility and acceptability outcomes, the assessment and progression criteria are summarized in Additional file 4: Table S1. The progression criteria provided below are based on the evidence [38, 39], results from the systematic review by Yang et al. [24] and discussion with the stakeholders. The recruitment progression criteria to proceed with RCT was set at ≥ 50% of eligible participants consented to participate in the study in 3 months which was decided based on the findings from the survey. The retention progression criteria to proceed with RCT were set at ≥ 83% (40/48) of the participants submitting the baseline questionnaires, while ≥ 79% (38/48) of the participants submit at the first follow-up time point and ≥ 75% (36/48) of the participants submit at the second follow-up (42-day after delivery). The adherence progression criteria need to be assessed from two perspectives including ≥ 75% (18/24) of the participants complete at least 75% (3/4) of the face-to-face sessions and ≥ 75% (18/24) of the participants perform PFMT twice a day at home and record it on the training diary. The progression criteria for the acceptability and delivery of the intervention were the participants and the midwife had strongly positive views on their participation in the intervention. The feasibility study will proceed with a RCT if the above progression criteria are met. The progression criteria for proceeding with changes and stopping to proceed to a further study were provided in detail in Additional file 4: Table S1.

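### The protocol places the baseline assessment after randomization, so knowledge of allocation can affect self-reported baseline UI and whether the baseline is completed

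*Protocol article*

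**What the plan says.** Four places in the protocol article bear on when baseline is taken.

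- Recruitment section, first paragraph on consent procedures: after signing the consent form, women move to a different room, where "they will meet the research midwife in another office in the hospital and complete the baseline data". Randomization has not yet been described.
- Recruitment section, next paragraph: after the block randomization and the sealed envelopes, "The envelope will be offered to the participants in sequence by the midwife", and directly after that, "They will complete the baseline assessment after randomization". The following sentence schedules women in the group arm for their first session.
- The heading of that section: "Recruitment, consent, assessments, randomization and allocation concealment". It names assessments before randomization.
- Measures: baseline measures "will be collected after obtaining informed consent from the participants". Randomization is not mentioned.

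On what is measured, Measures says that "the UI outcome measures include self-reported UI and UI severity will be assessed by ICIQ-SF", and Study design makes baseline the first of three assessment points. The Blinding section says that the midwife delivering the intervention cannot be blinded and that the principal researcher is blinded while analysing the feasibility data. It does not say that participants are blinded. The retention progression criteria include at least 83% (40/48) "of the participants submitting the baseline questionnaires".

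**The concern.** A baseline measure describes the women as they were before the trial could influence them. If a woman learns her arm first, her baseline becomes a post-randomization measurement. The two arms are easy to tell apart: one offers four group sessions with diaries and a chat group, the other verbal instruction only. A woman who knows her arm may rate her leakage differently, or may be less inclined to return the form.

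Three things are at stake.

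- **UI status at entry.** The study enrols women with or without UI symptoms and its title covers both prevention and treatment. The baseline questionnaire is what would describe that mix.
- **Baseline completion as a result.** Completion of questionnaires is one of the feasibility outcomes and carries its own progression threshold. If allocation can drive non-return, the figure mixes willingness to fill in the form with reaction to the allocated arm.
- **The procedure carried forward.** A feasibility study rehearses the main trial, and the definitive trial would inherit this order of steps.

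**Working it through.** **Step 1. Compare the two possible orders with the text.**

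- *Order A: consent, baseline, envelope.* This fits the paragraph on consent, the order of terms in the heading, and Measures. It conflicts with the sentence that puts baseline after randomization.
- *Order B: consent, envelope, baseline.* This fits that sentence and Measures. It also fits the paragraph on consent if the reader assumes that an envelope step, not mentioned there, comes between consent and baseline. It does not fit the order of terms in the heading.

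No statement in the article expressly puts baseline before allocation. The only sentence that relates baseline to randomization puts it afterwards. Under order A the text contradicts itself. Under order B it is roughly consistent, but baseline is post-randomization. Either way the sentence needs correcting.

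**Step 2. Does the baseline include the self-reported UI measure?**

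This is inferred, not stated in one place. Study design counts baseline as an assessment point, Measures gives a completion time for the UI measure on each occasion, and the progression criteria refer to baseline questionnaires. The assessment schedule (Fig. 2) and the participant flow (Additional file 2) are not available here. The opening of the envelope is not described either; that a woman knows her arm by then follows from the sentence order and from the words used about randomization.

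**Step 3. The one figure attached to baseline.**

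Inputs: total sample 48, with 24 per arm (Sample size); threshold 40/48 (progression criteria, in Measures).

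- The protocol's own figure: 40/48 = 83.3%, which agrees with the stated 83%.
- Missing forms compatible with the threshold: 48 − 40 = 8, and 8/48 = 16.7%.
- If the 8 were spread evenly: (24 − 4)/24 = 20/24 = 83.3% in each arm.
- If all 8 were in one arm: (24 − 8)/24 = 16/24 = 66.7% there, against 24/24 = 100% in the other.

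Both patterns give 40/48, so the pooled criterion cannot tell them apart. An imbalance by chance could arise under either order. Only when baseline follows allocation can knowledge of the arm cause it.

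**Step 4. Does any planned analysis use the baseline value?**

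Data analysis names descriptive statistics, the Mann–Whitney test and the chi-square test. It names no baseline covariate, no change score and no subgroup by baseline UI. It says that the group comparison serves to obtain standard deviations and a sample size for the definitive trial, and Discussion says that the data will not be used to assess effectiveness.

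**The case against.** The strongest reply has four parts.

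*The passages can be reconciled.* Consent, envelope, baseline satisfies both sentences of the recruitment section, if awkwardly, and the figure and additional file that might settle the order are not shown. This stands in part: the contradiction is partly implicit. But that reading confirms that baseline is taken after allocation.

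*Nothing planned depends on baseline.* This stands. A reader might infer that the treatment comparison will be biased. The article plans no baseline-adjusted or change-score analysis and disclaims any conclusion on effectiveness. It does mention looking for evidence of promise, but attaches no baseline-dependent analysis to it.

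*The standard deviation is safe.* A reader might also infer that the standard deviation carried into the definitive trial would be distorted. The article does not say that the baseline standard deviation is the one carried forward, and a constant shift in one arm's answers leaves the within-arm standard deviation unchanged. The documents do not support that inference.

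*The 40/48 threshold is a progression criterion.* It would exist under either order, does not permit baselines to be left uncollected, and says nothing about whether missing forms differ by arm. This also stands. The arm split in the working shows only what the pooled figure would fail to reveal.

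What remains is the order of steps itself, and its effect on baseline description, baseline completion and the procedure for the next trial.

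**Conclusion.** The concern holds in this form: the protocol states that baseline is completed after randomization, other parts of the article suggest the reverse, and with self-reported UI and no stated participant blinding the stated order leaves baseline answers and baseline non-completion open to influence by allocation.

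The consequence is moderate. It touches the description of UI status at entry, the meaning of the baseline completion rate, and the procedure handed to the definitive trial. It does not touch a planned effectiveness or baseline-adjusted analysis. The size of any reporting shift cannot be obtained from the document and none is claimed. For completion, the outer bound is 16/24 against 24/24 with the pooled criterion met.

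The conclusion assumes that the UI questionnaire is part of the baseline assessment, that a woman knows her arm once she has been randomized, and that the schedule and flow documents not shown here do not already fix a different order. Rating: should be fixed.

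**What to change.** 1. In the recruitment section, replace the sentence that puts baseline after randomization with one stating that demographics and the UI questionnaire are completed after consent and before the envelope is opened.
2. In Measures, extend the statement on timing so that it gives both limits: after consent and before allocation is revealed. Check the SPIRIT schedule (Fig. 2) and the participant flow (Additional file 2) against the same order.
3. Do not make a fully complete questionnaire a condition of randomization. Such a gate would make baseline completion 100% among randomized women by construction. It would empty the baseline criterion, and the baseline part of the missing-items measure in Table 1, of information. Keep counting missing items.
4. State the denominator of the 40/48 baseline criterion, for example consented women, and report baseline completion by arm as well as pooled.

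The cost is wording and the order of two steps. No extra participants or assessments are needed. The article does not say at which visit the envelope is offered, so the site should confirm that the new order fits its visits. The trial had not started recruiting when the article was submitted. If recruitment has since begun, the order actually used for each woman should be recorded and reported.
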